### Implementation {16c}

The allocation sequence was provided by the online randomisation service. The allocation is generated once participant eligibility criteria are entered into the platform by clinical research coordinators blinded to any allocation.

## Assignment of interventions: blinding

### Who will be blinded {17a}

Due to the nature of the intervention, participants and the research team delivering the intervention will not be blinded to the treatment received. Those involved in the data analyses and statistics will be blinded to the group allocation.

### Procedure for unblinding if needed {17b}

There are no required processes as the trial is open label.

## Data collection and management

### Plans for assessment and collection of outcomes {18a}

The data collection team consists of research assistants who will collect key outcome. A study specific case report form (CRF) has been designed for collection of all related data required to analyse the study outcomes. The data is mostly captured on electronic medical records and copied into the CRFs on a periodic basis by the research assistants. The study investigators regularly scrutinise the data for any inconsistencies or missing information. The forms are maintained in the patient files and an electronic copy is fed into the study database for future analyses.

### Plans to promote participant retention and complete follow-up {18b}

A robust plan aims to encourage app use and all technical problems are resolved expediently by the technical team. Regular contact with trial participants will ensure retention.

### Data management {19}

All personal data will be coded, and all patients enrolled into the study will be given a unique and confidential participant ID only accessible to the research team. The unique IDs and data collected will be stored in the database in an encrypted format. The database that contains personal information of the patient will be kept separate from the database containing their health information. The only connection between the databases will be the unique Identifier which again will be encrypted throughout the study and during data transmission. The data entered by study participants will be directly sent over a secure line to the database for storage. There will be no third party involved in the transmission of data. Coded data without the allocation will be provided for data analysis.

### Confidentiality {27}

All identifiable data will be kept securely in locked cabinets in a locked room. Electronic data will be kept encrypted on secure servers with specific log access by research personnel. The authorised personnel will only be able to access the minimum necessary information needed to perform job functions.

### Plans for collection, laboratory evaluation and storage of biological specimens for genetic or molecular analysis in this trial/future use {33}

Blood samples collected during the study shall be used for the purpose of this trial alone. Any leftover samples will be discarded at the end of the study.

## Statistical methods

### Statistical methods for primary and secondary outcomes {20a}

Descriptive statistics will be used to summarise and determine the sample characteristics and distribution of patients’ data. The normally distributed data and results will be reported with mean and standard deviation (SD) with corresponding 95% confidence interval (CI); the remaining results will be reported with median and inter-quartile range (IQR). Categorical data will be summarised using frequencies and proportions. Associations between two or more qualitative data variables will be assessed using chi-square (*χ*^2^) test or Fisher exact test, as appropriate. Quantitative data between the two independent groups will be analysed using unpaired *t* or Mann-Whitney *U* test as appropriate.

The analysis will follow the intention to treat principle with last observation carried forward. Difference in mean change from baseline HBA1c between the intervention arm and the standard care arm at 3 and 6 months will be analysed using repeated measure ANOVA method, linear regression and analysis of covariance (ANCOVA) methods as appropriate. Sensitivity analysis will be conducted using other approaches based on data available. Comparisons will be conducted between trial group and the observational cohort using the approaches described above.

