### Criteria for discontinuing or modifying allocated interventions {11b}

Participants may withdraw from the study at any time without their treatment or access to services being affected. Investigators may withdraw participants if they develop a condition that excludes them from the study, e.g. cancer.

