### Strategies to improve adherence to interventions {11c}

Participants are contacted in a timely manner to ensure they are reminded of their laboratory investigations and physician's appointments together with the dietitian and educator appointments. Also, the intervention group receive reminders from the healthcare providers on the mobile app. Any difficulties in using the app will be addressed by the healthcare provider and app technical team.

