### Sample size {14}

The initial sample size was based on a clinically relevant difference in HbA1c of 0.5% (5.5 mmol/mol) with SD 1% (11 mmol/mol) between the intervention and the standard care arms [26]. To achieve an 80% power and a significance level of < 0.05, 64 participants would be required in each arm. Assuming a 40% loss to follow-up, 90 participants were planned to be recruited in each arm. However, review of baseline characteristics of recruited participants by the trial steering group identified a higher SD of 1.7% (19 mmol/mol) giving 182 participants per arm, with a total recruitment of 608 participants to include a 40% dropout. Therefore, it was decided to extend recruitment beyond the initially planned number to 608 participants. Sample size calculations were made using STATA 15 MP. For the population cohort comparator group, we aim to select a sample 200 patients identified through the available diabetes registries to examine the impact of trial arms compared to a non-randomised group.

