### Methods in analysis to handle protocol non-adherence and any statistical methods to handle missing data {20c}

The data related to participants who voluntarily withdraw from the study or lost to follow-up (non-adherence) shall be analysed with an “intention to treat” analysis.

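### Last observation carried forward as the primary missing-data rule, with 40% dropout planned, can bias the 6-month HbA1c difference in either direction

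*Protocol article*

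**What the plan says.** Under Statistical methods for primary and secondary outcomes {20a}, the protocol article says: "The analysis will follow the intention to treat principle with last observation carried forward". The next sentence applies this to the between-arm difference in HbA1c change, which "at 3 and 6 months will be analysed using repeated measure ANOVA method, linear regression and analysis of covariance (ANCOVA) methods as appropriate". The only stated safeguard is "Sensitivity analysis will be conducted using other approaches based on data available". The section on non-adherence and missing data {20c} repeats intention to treat for those who withdraw or are lost, and names no other method.

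Sample size {14} gives 182 evaluable participants per arm, "with a total recruitment of 608 participants to include a 40% dropout". The primary outcome {12} is the between-arm difference in mean HbA1c change at 6 months.

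**The concern.** The article itself fixes this rule for the primary outcome, so it is not a detail left to an unseen analysis plan. With analyses at 3 and 6 months, the carried value is either baseline (change of zero) or the 3-month value.

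Two features of the protocol make a fall in both arms plausible. Entry requires HbA1c of at least 8.5% (Eligibility criteria {10}), which invites regression to the mean. The choice-of-comparator section {6b} also expects comparator groups to gain from taking part in a trial. If both arms fall, carried values are too high, and the arm that loses more participants looks worse.

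Dropout may differ between arms. The trial is open-label, and one retention measure reaches one arm only: "Also, the intervention group receive reminders from the healthcare providers on the mobile app".

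At stake is the primary estimate. The rule could shrink a real effect, create one where none exists, or hide one, and nobody can say beforehand which will happen.

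**Working it through.** **The plan's own figure.** Inputs from Sample size {14}: difference 0.5, SD 1.7, 80% power, 5% level (two-sided reproduces the figure), 40% dropout.
- n per arm = 2 × (1.96 + 0.84)² × 1.7² / 0.5² = 181.5, so 182.
- 182 / 0.6 = 303.3, so 304 per arm and 608 in total. Both reproduce.
- Expected observed at 6 months: 304 × 0.6 = 182.4 per arm. Expected carried: 304 × 0.4 = 121.6 per arm.

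The inflation treats dropouts as giving no 6-month information, whereas the planned analysis uses all 304.

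**Assumptions (not in the documents).** Control fall F at 6 months is 0.5 or 1.0, with 70% of it reached by 3 months. The 3-month treatment effect is 60% of the final effect. A share q of dropouts leaves before 3 months (half or all). Baseline to follow-up correlation is 0.5, so the change SD is 1.7 × √(2 × 0.5) = 1.7. Dropout is unrelated to outcome.

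**Formulas.** For an arm with dropout d and mean changes m3 and m6:
- M = (1 − d)·m6 + d(1 − q)·m3
- V = (1 − d)(1.7² + m6²) + d(1 − q)(1.7² + m3²) − M²
- SE of the difference = √((V_app + V_control) / 304)

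**Dilution: true effect 0.50, 40% dropout in both arms.**
- All lost early: 0.6 × 0.50 = 0.30.
- Half lost early: 0.6 × 0.50 + 0.2 × 0.30 = 0.36.

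If dropouts already have the full effect at 3 months, there is no dilution.

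**Power, like for like (F = 1.0).**
- Change score on observed data: SE = 1.7 × √(2/182.4) = 0.178; power 80%.
- Change score with values carried, all lost early: V_control = 0.6 × 3.89 − 0.60² = 1.974; V_app = 0.6 × 5.14 − 0.90² = 2.274; SE = √(4.248/304) = 0.118; power = Φ(0.30/0.118 − 1.96) = 72%.
- Half lost early: SE 0.130; power 79%. With F = 0.5 the two values are 77% (all early) and 82% (half early).
- ANCOVA on observed data: SE = 1.7 × √0.75 × √(2/182.4) = 0.154; power 90%. ANCOVA with values carried, by simulation: about 85 to 87% (half early) and 77 to 79% (all early).

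Simulated change-score power (about 77% and 74%) is within about two points of the closed form at F = 1.0.

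**False effect: no true effect, unequal dropout (change score).** The first figure is half lost early, the second all lost early.

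| Shared fall F | Dropout app / control | False benefit | Type I error |
|---|---|---|---|
| 0.5 | 35% / 45% | 0.03 to 0.05 | 6% to 7.5% |
| 0.5 | 30% / 50% | 0.07 to 0.10 | 8% to 15% |
| 1.0 | 35% / 45% | 0.07 to 0.10 | 8% to 14% |
| 1.0 | 30% / 50% | 0.13 to 0.20 | 18% to 42% |

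Example, last row, all early: 0.70 × 1.0 − 0.50 × 1.0 = 0.20. Reversing the dropout rates reverses the sign. Analysis of observed data stays at about 4 to 6% in these null scenarios.

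**A real effect hidden.** True effect 0.50, F = 1.0, dropout 50% app and 30% control, all early: 0.50 × 1.5 − 0.70 × 1.0 = 0.05.

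**Standard error.** By ANCOVA it is about 0.11 to 0.12 with values carried (F = 1.0), against 0.154 from observed data.

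**The case against.** Several stronger readings are tempting, and the documents do not support them.

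- *The carried-forward standard error is wrong.* It is right for its own estimator: in simulation the model standard error matches the sampling SD (0.117 against 0.118), and type I error is about 5% with equal dropout and no effect. What stands is that counting carried values as 6-month data overstates how precisely the 6-month difference is known.
- *Power collapses.* Setting a change-score test on carried values (72 to 80%) against ANCOVA on observed data (89%) mixes two effects. Most of that gap is baseline adjustment, which {20a} also allows.
- *Dropout will differ by arm.* The adherence section {11c} describes appointment and laboratory reminders without limiting them to one arm, the retention section {18b} promises regular contact with participants, and standard care plans at least three-monthly visits. Withdrawal by investigators ("Investigators may withdraw participants if they develop a condition that excludes them from the study, e.g. cancer") is not tied to an arm. Unequal dropout is possible, not established.
- *Type I error will be near 40%.* That is one corner of the assumed scenarios; milder inputs give 6 to 8%.
- *A named sensitivity analysis is missing.* The article commits to sensitivity analysis, and the analysis plan, which is not shown, may name the method.

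It is also fair that 40% is an allowance rather than an observed rate, that some missing values may be recoverable from records, and that carrying forward is not biased for participants who truly return to the carried value. None of this makes the rule a sound primary choice.

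**Conclusion.** The point holds as a fault in a stated method. At the dropout the protocol plans for, carrying values forward can dilute a true 0.50 to about 0.36 to 0.30, or move the estimate towards or away from the app according to which arm loses more.

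Dilution requires loss before 3 months or a smaller effect at 3 months than at 6. A false effect requires both unequal dropout and a change shared by the arms. The protocol makes the shared change likely and unequal dropout possible, but gives no size for either. The loss of power is secondary: on a change-score test, from 80% to between 79% and 72% with a shared fall of 1.0, and little or none with a fall of 0.5. The case rests on bias of unknown direction in the primary estimate. The comparison with observed data assumes that dropout is unrelated to outcome.

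**What to change.** In {20a}, replace last observation carried forward as the primary rule with one of these:

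- a likelihood-based repeated-measures model of 3- and 6-month HbA1c in all randomised participants, with arm, visit, arm-by-visit, baseline HbA1c and the minimisation factors; or
- multiple imputation by arm that uses the 3-month value.

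Name the 6-month contrast as the primary test and keep the carried-forward analysis at most as supportive.

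Use 6-month HbA1c values already in the medical record for participants who stop the intervention, where consent allows. The collection section {18a} shows that the route exists: "The data is mostly captured on electronic medical records and copied into the CRFs on a periodic basis by the research assistants".

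The cost is a change of wording, a little programming and a record look-up. The target of 608 stays, since it already rests on 182 observed per arm. The reported standard error will be larger than with carried values. Either method still assumes that dropout is explained by the data observed. The change should be made before any analysis by arm, so that it cannot look data-driven.

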### Trial design {8}

QDMAT is an ongoing open-label parallel group randomised clinical trial. Participants with T2DM who are treated with insulin will be randomised with a 1:1 ratio into an intervention arm and standard care arm. Participants in the intervention arm will receive care through the Droobi mobile app in addition to their standard care. Participants in the control group will receive the usual DM care based on national and international DM care guidelines [22, 23].

A diabetes population comparator group will be used to examine the natural progression of diabetes and its treatment outside the randomised controlled trial. This population will contextualise and determine the effectiveness of the trial arms compared to a non-randomised population.

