### Eligibility criteria {10}

#### Inclusion criteria

The following will be included in QDMAT:Adults with T2DM (based on clinical records);18–60 years of age;Uncontrolled DM with HBA1c ≥ 8.5% (69 mmol/mol);Insulin treated T2DM;Arabic or English language speaking and able to read and write in one of these languages;Possession of a smart mobile phone and willing to use a smart phone app;Able to communicate via chat with the mobile app team through the app as evidenced by at least weekly use of any of the social media apps;Willing to utilise a mobile application for DM management.

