## Interventions

### Explanation for the choice of comparators {6b}

The comparator group with be standard diabetes care following national and international guidelines [22, 23]. Since in clinical trials, the comparator group often benefits from improved outcomes through trial participation, as part of the study, an observational matched diabetes population comparator group will also be examined using data from electronic medical records. This will contextualise and determine the effectiveness of the trial arms compared to a non-randomised population.

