#### The healthcare provider team

Mobile app intervention team: This team consists of healthcare providers comprising of physician, diabetes educators and dietitians who provide feedback and coaching to participants through the app using all clinical and self-entered information available within the app.

Standard care team: This team consists of healthcare providers comprising of physician, diabetes educators and dietitians providing standard diabetes care based on national and international diabetes guidelines.

Insulin doses were adjusted based on multi-professional assessment to avoid any risks associated with hypoglycaemia.

For the observational comparator population, patients records will be identified via electronic medical records to match inclusion/exclusion criteria of QDMAT participants.

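### A non-randomised registry cohort of 200 is given an effectiveness role, but the plan describes matching on eligibility only and does not commit to adjusting for confounders

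*Protocol article*

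**What the plan says.** The role of the cohort is stated twice in the protocol article. Trial design {8} says "This population will contextualise and determine the effectiveness of the trial arms compared to a non-randomised population", and Explanation for the choice of comparators {6b} repeats it: "This will contextualise and determine the effectiveness of the trial arms compared to a non-randomised population".

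Three sections describe how the cohort is formed:
- Explanation for the choice of comparators {6b}: "an observational matched diabetes population comparator group will also be examined using data from electronic medical records".
- The healthcare provider team: "patients records will be identified via electronic medical records to match inclusion/exclusion criteria of QDMAT participants".
- Sample size {14}: "we aim to select a sample 200 patients identified through the available diabetes registries". No effect size, power or precision is given for this number.

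The analysis is set in Statistical methods for primary and secondary outcomes {20a}: "Comparisons will be conducted between trial group and the observational cohort using the approaches described above". The methods that precede this sentence are chi-square or Fisher tests, unpaired t or Mann-Whitney tests, intention-to-treat with LOCF, and repeated-measures ANOVA, linear regression and ANCOVA where appropriate. The HbA1c methods are worded for the intervention arm against the standard care arm.

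The section on exploratory outcomes and additional analyses lists the comparison with the cohort.

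**The concern.** Between the randomised arms, a two-group test of change in HbA1c is valid without adjustment because allocation takes care of confounding in expectation. Between a trial arm and a set of patient records it is not. Trial participants volunteered, gave consent, own a smartphone and agreed to use an app; cohort members were found in a database. The plan carries the first setting's methods into the second and does not say that the adjusted ones must be used.

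The article itself justifies the cohort by noting that trial comparators often improve through taking part. An unadjusted contrast cannot separate that effect from the kind of patient who volunteers. At stake is what may be concluded: a difference between a trial arm and the cohort could be published as evidence of effectiveness with the protocol's backing, although part or all of it may reflect who was selected.

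**Working it through.** **1. What the matching delivers.** Set side by side, {6b} promises a matched group, while The healthcare provider team section describes only choosing records that meet the inclusion and exclusion criteria. That is restriction. It gives both groups the same age limits, insulin treatment and HbA1c threshold (8.5% or above), but does not balance age, diabetes duration, regimen or HbA1c within those limits.

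**2. Whether eligibility can be reproduced.** Inclusion criteria include "Possession of a smart mobile phone and willing to use a smart phone app" and "Willing to utilise a mobile application for DM management", plus at least weekly social-media use. Routine records are unlikely to hold these. Consent to the trial is by definition absent in the cohort.

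**3. What the analysis rule commits to.** Of the methods listed in {20a}, linear regression and ANCOVA can adjust for confounders; the t, Mann-Whitney, chi-square and Fisher tests cannot. The choice is left open, and for the cohort contrast no confounder is named and no adjustment is required.

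**4. The plan's own figures.** The cohort size of 200 has no inputs, so it cannot be reproduced. The trial figures in Sample size {14} can, with two-sided alpha 0.05 and 80% power:
- n per arm = 2 × (1.960 + 0.842)² × 1.7² / 0.5² = 181.5, so 182, as stated.
- With 40% dropout: 182 / (1 − 0.4) = 303.3, so 304 per arm and 608 in total, as stated.

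**5. Illustration of size.** Assumption: the SD of 1.7%, which the article takes from baseline data, also applies to the outcome compared.

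SE = 1.7 × √(1/200 + 1/n), where n is the size of the trial arm.
- n = 304: SE = 0.155; 95% CI half-width = 1.96 × 0.155 = 0.30 points.
- n = 182: SE = 0.174; half-width = 0.34 points.

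If there is no true difference but a residual bias b remains, the two-sided false-positive rate is 1 − Φ(1.96 − b/SE) + Φ(−1.96 − b/SE):

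| Assumed b (HbA1c points) | 200 vs 304 | 200 vs 182 |
|---|---|---|
| 0 | 5% | 5% |
| 0.1 | 10% | 9% |
| 0.2 | 25% | 21% |
| 0.3 | 49% | 41% |

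The values of b are assumptions, not document figures. All are below the 0.5% that the article treats as clinically relevant.

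**The case against.** The strongest reply is that the plan is not as bare as it may look. Restriction to the eligibility criteria is a form of control, and regression and ANCOVA are already listed. The comparison is exploratory, the stated purpose includes giving context, and the primary outcome rests on the randomised arms alone. A journal article may also leave covariate lists and index dates to the full protocol or analysis plan. The Discussion adds that people with diabetes in Qatar often use technology for health purposes, which suggests, without proving, that selection on phone use may be modest. All of this stands and limits the point.

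It also rules out several stronger readings that a reader might infer:
- *There is no confounding control.* The documents do not support this; restriction is described and adjustment is possible. What is missing is a commitment to it.
- *A cohort of 200 is too small to match the arms.* One-to-one matching is never promised, and the evaluable number required is 182 per arm, fewer than 200.
- *The cohort does not share the arms' regression to the mean.* Cohort members must also meet HbA1c of 8.5% or above. The article does not say when that value is taken, so this cannot be asserted.
- *A baseline HbA1c imbalance will carry a known bias into the result.* ANCOVA on baseline HbA1c would remove that component, so any such figure applies only to unadjusted comparisons.

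The reply does not remove the claim in {8} and {6b}, the mismatch between matched and eligibility-only selection, or the rule in {20a}. These are statements in the text, not omissions left to another document.

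**Conclusion.** The point holds in limited form. The article gives a non-randomised cohort the job of establishing how effective the arms are, describes selection on eligibility alone, and applies the methods of the randomised comparison without requiring adjustment. Following it as written can produce a confounded contrast presented as effectiveness evidence.

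The size of any bias is unknown. The false-positive rates of about 10% to 49% depend on an assumed residual bias of 0.1 to 0.3 points, the SD of 1.7%, 200 against 304 patients, and an unadjusted test. Even a good adjustment would leave willingness to use an app and consent uncontrolled, so the effectiveness wording is too strong whichever method is used. The change should be made, but the trial's primary conclusion does not depend on it.

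**What to change.** - **Statistical methods {20a}:** replace the sentence that carries the earlier methods over to the cohort. Commit to a covariate-adjusted or propensity-weighted comparison on age, gender, diabetes duration and insulin regimen (the minimisation factors in Sequence generation {16a}), baseline HbA1c and calendar time. Report adjusted differences with 95% CIs, and do not base inference on unadjusted tests.
- **Trial design {8} and Explanation for the choice of comparators {6b}:** replace the statement that the cohort will establish effectiveness with one that it will *describe the trial arms in context*.
- **{6b} and The healthcare provider team:** reconcile the two, either by saying that matched means meeting the eligibility criteria or by naming the matching variables.
- **Limitations of the comparison:** name app willingness and trial consent as unmeasured confounders.

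The cost is a little more analysis work and a weaker claim for the cohort comparison. The cohort can stay at 200, and no participants or trial procedures are added.
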